## Methods

### Study Design

We are conducting a monocenter 2-arm randomized controlled trial with 3 assessment points (baseline, postintervention at 8 weeks, and follow-up at 6 months). Participants in the intervention condition will receive access to MindDoc with Prescription in addition to care as usual. Participants in the control condition will only have access to care as usual. Care as usual includes any form of treatment, including psychotherapy, unless psychotherapy has already been started or planned at the time of inclusion in the study. The study design is illustrated in Figure 1.

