After the baseline survey has been completed, participants are randomized at the person level with 1:1 group assignment. Randomization is performed as block randomization in blocks of 4, 6, and 8, stratified by sex (male, female, and diverse), diagnosis (F32.0, F32.1, F33.0, and F33.1), and previous psychiatric or psychotherapeutic treatment (yes and no). Randomization lists were generated (1 per stratum) using Sealed Envelope [51] and directly integrated into the EDC system. Randomization is performed in a protected area of the EDC system that can only be accessed by authorized members of the study team without them having access to the randomization lists.

Participants will be notified of the results of the assignment via email. Participants assigned to the intervention group will immediately receive free access to the DiGA described below. Participants in the control group will receive free access to the DiGA after they complete their follow-up assessment.

In both groups, postintervention and follow-up assessments will take place after 8 weeks and after 6 months. The links to the respective surveys are sent to the participant’s email address. The postintervention assessment also includes another telephone interview which is conducted by a clinical psychologist or clinical psychologist in training. Interviewers are blinded to the group assignment of the study participants.

If a participant fails to respond to a survey invitation, up to 5 reminders are sent within 14 days. If no response has been received after 28 days, the assessment will be marked as missing.

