##### Other Measures

Depression symptom severity will also be rated by a clinician (clinical psychologist or clinical psychologist in training), using a short version of the Hamilton Rating Scale for Depression (HAM-D) with 6 items. The chosen version best differentiates between groups with and without treatment compared with other versions [62]. HAM-D is the most widely used clinician-administered depression assessment scale. The rating scale was supplemented with the Structured Interview Guide for the HAM-D (SIGH-D) [63,64]).

The therapeutic alliance is measured with a shortened version of the Working Alliance Inventory (WAI-SR) [65] is used, which contains the 8 items of the dimensions (process and goals).

Negative intervention effects were assessed with the Inventory for Balanced Assessment of Negative Effects of Online Interventions (INEP-ON) [66], which captures negative intervention effects from the patient’s perspective. The questionnaire also assesses whether patients attribute these effects to the intervention or to other factors.

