### Statistical Analysis

Data will be described using descriptive statistics (eg, frequencies, mean, median, SD, and IQR) and visualizations (eg, histograms, box plots, and bar charts). Assumptions for statistical tests will be checked (eg, normality by histograms and tests, sphericity by Mauchly test, and equal variance-covariance matrices by Box and Levene tests). App usage will be described according to previously proposed standards for reporting adherence to digital interventions [69], and include days of use and engagement with different features of the app.

Significant baseline group differences will be detected using *χ*^2^ and *t* tests on baseline variables and accounted for in all analyses.

The intervention’s effectiveness will be analyzed using an intention-to-treat approach with multiple imputed data. Missing values from the postsurvey and follow-up survey of nonbinary end points will be imputed using all available information collected at baseline by applying an iterative Markov chain Monte Carlo method based on the initial group assignment. For this purpose, imputations will be calculated for 100, 150, 200, 300, 400, and 500 iterations. Then, the fraction of missing information (FMI) index will be determined for all multiply imputed data sets. The FMI ranges from 0 to 1 (where 1 means that 100% of the information required for the planned conclusions is missing) and is a reliable indicator of the validity of conclusions based on imputed data sets [70]. For the following analyses, the number of imputations that do not result in further improvement in FMI compared to previous imputations will be chosen. Statistical characteristics will be aggregated across the multiply imputed data sets using Rubin’s rules. The comparison of intervention effects on all outcomes will be done using *t* tests.

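### Imputing from baseline data and group alone leaves the observed 8-week scores out of the 6-month imputation, which can bias the 6-month effects if response-related dropout differs between arms

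*Protocol article*

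**What the plan says.** The Statistical Analysis section specifies the imputation in one sentence. Its targets are "Missing values from the postsurvey and follow-up survey of nonbinary end points", so both later time points are covered. These values "will be imputed using all available information collected at baseline", "by applying an iterative Markov chain Monte Carlo method based on the initial group assignment". The results are pooled by Rubin's rules, and "The comparison of intervention effects on all outcomes will be done using *t* tests".

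The article describes post-baseline information that this sentence does not name:

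- Study Design sets assessments at baseline, 8 weeks and 6 months, so an 8-week score will exist for some participants who miss the 6-month survey.
- Under Procedures, the surveys come by emailed link, but "The postintervention assessment also includes another telephone interview which is conducted by a clinical psychologist or clinical psychologist in training". The interviewers are blinded.
- Under Other Measures, severity is rated in addition by a clinician, "using a short version of the Hamilton Rating Scale for Depression (HAM-D) with 6 items".

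On the amount of missing data, Sample Size plans for dropout of up to 60%. Results reports about 20% missing in the primary outcome so far. No rate is given for 6 months.

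**The concern.** The best predictor of a missing 6-month PHQ-9 is usually the same person's 8-week PHQ-9. A model that conditions only on baseline and arm assumes that, given those, people who stop responding would have scored like those who stay. A model that also conditions on the 8-week score allows dropout to depend on how the person was doing at 8 weeks, which is a weaker assumption and uses data already collected.

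Only one arm has the app, so dropout related to response could well differ between arms. The baseline-only model would then carry the difference into the 6-month treatment effect. Even without bias, it discards information. The article says that the trial is meant to support a reimbursement listing, so the 6-month estimates should not rest on an assumption that is stronger than necessary.

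**Working it through.** **The plan's own figure.** For d = 0.4, 85% power and two-sided α = 5%, the t-based sample size is 114 per arm. Then 2 × 114 = 228, and 228 / (1 − 0.60) = 570, as stated. The 60% is therefore a planning ceiling. It is not an observed rate.

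**Set-up for the 6-month effect.** The documents give no correlations and no dropout mechanism. All of the following are assumptions:

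- correlation of baseline with each later score: 0.4
- correlation of 8 weeks with 6 months: 0.65
- true effect: 0.30 SD in favor of the app
- dropout in the app arm: log-odds rise with the 8-week score (poor responders leave), odds ratio 1.5 or 2 per SD
- dropout in the control arm: unrelated to the 8-week score, same overall rate

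**Hand approximation.** After removing baseline, the residual covariance between the 8-week and 6-month scores is 0.65 − 0.4 × 0.4 = 0.49. Under logistic dropout with log-odds slope β on the 8-week score, missing and observed participants differ in their 6-month residual by about 0.49β. Baseline-only imputation sets this difference to zero for the missing share m, so

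bias ≈ m × 0.49 × β.

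- OR 1.5, β = ln 1.5 = 0.405: at m = 0.2 the bias is 0.2 × 0.49 × 0.405 = 0.04, giving 0.34. At m = 0.6 it is 0.12, giving 0.42.
- OR 2, β = ln 2 = 0.693: at m = 0.2 the bias is 0.07, giving 0.37. At m = 0.6 it is 0.20, giving 0.50.

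**Large-sample simulation** of the same set-up (within-arm regression imputation, 1 to 2 million per arm) agrees closely. The approximation runs slightly high at OR 2.

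| Missing at 6 months | Baseline-only estimate, OR 1.5 to 2 (true 0.30) |
|---|---|
| 20% | 0.34 to 0.36 |
| 40% | 0.38 to 0.42 |
| 60% | 0.41 to 0.49 |

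**Opposite direction.** If good responders leave the app arm, the estimate falls to about 0.24 to 0.26 at 20% missing and 0.11 to 0.18 at 60%.

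**Same mechanism in both arms.** With equal slopes and equal missing rates there is no bias. A second set of assumptions used correlations of 0.5 and 0.7, a log-odds slope of 1 per SD in both arms, a common intercept and a true effect of 0.40. It gave 0.38, 0.37 and 0.36 at 20%, 40% and 60% missing, an attenuation of 0.02 to 0.04 SD.

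**What adding the 8-week score recovers.** At 20% missing, with dependence in the app arm only:

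| Share of those missing at 6 months who have an 8-week score | Estimate (true 0.30) |
|---|---|
| 100% | 0.30 |
| 50% | 0.32 to 0.33 |
| 25% | 0.33 to 0.35 |

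**Primary end point, 8-week PHQ-9.** Here the extra predictors are the telephone HAM-D rating and, for late returners, the 6-month score. They help only participants who have one of these but no 8-week survey. The documents do not say how many there are, so no realistic size can be given.

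**The case against.** **The sentence may be looser than it reads.** An iterative method that handles both later time points together could let them inform each other, with the baseline clause naming only the auxiliary variables. That is possible. But the sentence names a single source of information for both time points, and the literal reading is the more natural one. New wording would settle it.

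**Sensitivity analyses are promised.** The Abstract announces additional imputation strategies, and a condensed article may leave their detail to an analysis plan that is not shown. This is fair, but a sensitivity analysis does not change the main estimate. The analyses described in the article do not repair the problem either: the ANCOVA adjusts for baseline only, and the per-protocol set excludes people who missed an assessment.

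**The mechanism is chosen.** Nearly all the bias comes from dropout that depends on response differently in the two arms. This stands, and the conclusion is worded accordingly.

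**Stronger readings that the documents do not support.** A reader might infer that any response-related dropout biases the results materially. It does not if both arms behave alike. A reader might also infer that adding the 8-week score always restores the true effect. That would need an 8-week score for everyone missing at 6 months, while about 20% already lack the primary outcome. Nor do the documents show that the primary result is substantially biased or could be fully corrected: the telephone call belongs to the same 8-week assessment as the survey, and its separate completion is not reported. Finally, the 60% rows show a ceiling, while the only reported rate is about 20%, at 8 weeks.

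**Conclusion.** The point holds for the 6-month secondary end points. As written, the imputation leaves out the observed 8-week scores and so relies on a stronger missing-data assumption than the data require. Where only the app arm's dropout depends on response, the distortion is roughly 0.04 to 0.06 SD at 20% missing and 0.11 to 0.19 SD at 60%, on a true effect of 0.30 SD. Its sign depends on whether poor or good responders leave. These sizes rest on the assumed correlations and dropout slopes. Using the 8-week scores reduces the bias in proportion to how many of those missing at 6 months have one.

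For the primary 8-week PHQ-9, the omission is a missed opportunity of unknown and possibly small size. The wording should be changed because the gain costs almost nothing, but the primary analysis is not shown to be wrong.

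**What to change.** Reword the imputation sentence before group-level data are analyzed, for example: *Missing 8-week and 6-month values of the continuous end points will be imputed jointly, by arm or with assigned group in the model, using baseline variables and all observed 8-week and 6-month outcome totals, with the 8-week HAM-D rating as an auxiliary variable.*

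Days of app use and post-baseline treatment use are optional. App data sit in a separate system, need merging and can be deleted by users (App Data section). A long predictor list may also be unstable: at 60% dropout only 285 × 0.4 = 114 observed outcomes per arm remain, against 3 × 4 × 2 = 24 randomization strata. These variables should be added only if the model stays stable.

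The cost is a revised sentence, a changed imputation script and a somewhat larger model. No new data are needed.

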### Sample Size

The primary end point is the between-group difference in depressive symptoms (PHQ-9 total score) after 8 weeks. The effect regarding the primary end point will be determined by a 2-tailed *t* test. Based on the results of our previous study, an effect of *d*=0.4 (Cohen *d*) is expected and a dropout rate of up to 60% is assumed. A sample size of 570 participants is required to detect the expected difference at 85% probability and α=5% significance in both intention-to-treat and per-protocol analyses.

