## Results

Recruitment for the trial started on February 7, 2023, and the first participant was randomized on February 14, 2023. As of September 5, 2023, a total of 275 participants have been included in the trial and 176 have provided the primary outcome. The rate of missing values in the primary outcome is approximately 20%.

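### The number of imputations is chosen by whether FMI improves, which tracks Monte Carlo noise; the effect is small, and one number fixed in advance removes it

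*Protocol article*

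**What the plan says.** All references are to the protocol article. Under Statistical Analysis, the intention-to-treat analysis uses multiply imputed data from a Markov chain Monte Carlo method. The selection procedure has four steps:

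- The grid: "imputations will be calculated for 100, 150, 200, 300, 400, and 500 iterations".
- The criterion: "Then, the fraction of missing information (FMI) index will be determined for all multiply imputed data sets". The article says of FMI that it "is a reliable indicator of the validity of conclusions based on imputed data sets".
- The choice: "the number of imputations that do not result in further improvement in FMI compared to previous imputations will be chosen".
- The pooling: Rubin's rules across the imputed sets, followed by t tests on all outcomes.

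The grid sentence speaks of iterations and the choice sentence of a number of imputations. The article gives no tolerance for what counts as an improvement. It does not say on which side of the stopping point the retained set lies, or which parameter's FMI decides.

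**The concern.** FMI measures how much information about a parameter is lost to missing data, given the imputation model. More imputations estimate it more precisely, but they do not recover lost information. A rule that waits for FMI to stop improving treats an almost constant quantity as if it had a trend. Its outcome is then set by simulation noise, and the set used for the primary analysis is picked by that noise from up to six candidates.

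FMI is computed from the between-imputation variance, which also enters the pooled standard error. Choosing on FMI can therefore select on the standard error as well. What is at stake is the reproducibility of the primary analysis and, under some readings, a slightly wrong standard error.

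Iterations (chain length) and imputations (number of completed data sets) are also different settings, and the text uses one grid for both.

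**Working it through.** The plan gives no figure for this rule that could be reproduced. Its one related calculation, the sample size, does reproduce: 114 per arm for d = 0.4, two-sided 5% and 85% power gives 228, and 228/(1 − 0.6) = 570.

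**Inputs.** The grid is m = 100, 150, 200, 300, 400, 500, read as numbers of imputations. FMI is not given, so a range is assumed: 0.2, matching the roughly 20% missing primary outcomes in Results; 0.6, matching the Sample Size section ("a dropout rate of up to 60% is assumed"); and 0.4 between them. Using a missingness rate as FMI is an assumption.

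**Step 1: systematic change in FMI.** With within-imputation variance U and between-imputation variance B, r = (1 + 1/m)B/U, df = (m − 1)(1 + 1/r)², and FMI = (r + 2/(df + 3))/(r + 1).

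Example for a true FMI of 0.2, so B/U = 0.25:

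- m = 100: r = 0.2525, df ≈ 2436, FMI = (0.2525 + 0.0008)/1.2525 = 0.2023.
- m = 500: r = 0.2505, df ≈ 12,435, FMI = (0.2505 + 0.0002)/1.2505 = 0.2004.

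**Step 2: noise in FMI.** B was simulated as its true value times χ²(m − 1)/(m − 1).

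| True FMI | FMI, m=100 → 500 | Fall | SD at m=100 | SD/fall |
|---|---|---|---|---|
| 0.2 | 0.2023 → 0.2004 | 0.0019 | 0.023 | about 12 |
| 0.4 | 0.4043 → 0.4009 | 0.0034 | 0.034 | about 10 |
| 0.6 | 0.6053 → 0.6011 | 0.0042 | 0.034 | about 8 |

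Each step up the grid lowers the estimated FMI with probability 0.50 to 0.51 if the six sets are independent, and 0.51 to 0.55 if smaller sets are nested in one run of 500.

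**Step 3: effect on the standard error.** The table gives the mean SE relative to its value at infinite m, as nested / independent.

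| Reading of the rule | FMI 0.2 | FMI 0.4 | FMI 0.6 |
|---|---|---|---|
| (a) keep the last improving set | 0.995 / 0.991 | 0.990 / 0.983 | 0.985 / 0.974 |
| (b) take the first non-improving set (literal) | 1.000 / 1.005 | 1.001 / 1.010 | 1.001 / 1.015 |
| (c) keep the lowest FMI | 0.993 / 0.988 | 0.987 / 0.976 | 0.980 / 0.964 |

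**Step 4: type I error at nominal 0.05, independent sets.**

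| Reading | FMI 0.2 | FMI 0.6 |
|---|---|---|
| (a) | 0.052 | 0.056 |
| (b) | 0.049 | 0.047 |
| (c) | 0.053 | 0.059 |

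Hand check for (a) at FMI 0.2: 1.96 × 0.991 = 1.943, two-sided tail 0.052.

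**Step 5: m fixed in advance.** At m = 500 the mean SE ratio is 1.000, with a 5–95% range of 0.990 to 1.011 at FMI 0.2 and 0.970 to 1.032 at FMI 0.6. At m = 100 the mean ratio is 1.001 to 1.002. Type I error is 0.050 in both cases.

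**The case against.** The case for leaving the text alone is a fair one.

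- **Every candidate is adequate.** If the grid is imputations, even the smallest set has 100, and at a fixed 100 the inference is sound. A reader might infer that the rule invalidates the primary analysis; Step 5 does not support that.
- **The direction of error is not fixed.** A reader might infer that the rule favours standard errors that are too small. That holds only if the last improving or lowest-FMI set is kept. The literal wording gives a standard error that is unbiased or slightly large. If improvement means stabilisation, the rule is a loose but harmless adequacy check.
- **The larger figures need unfavourable inputs.** They require an FMI of 0.6, the planning ceiling, while reported missingness is about 20%. Imputing from baseline information could push FMI below the missingness rate, and nested sets roughly halve the effect.
- **The choice is not described as outcome-driven.** A reader might infer that the analyst picks among results already seen. The stated order is to impute, determine FMI, choose the number, pool and test, and the criterion is neither the estimate nor the p value. FMI for the treatment contrast may require fitting that contrast, but the article does not describe comparing effects across sets.
- **An article condenses.** Seed, burn-in and convergence plots belong in the analysis plan, and their absence here is no fault.

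All of this limits the size of the point. It does not rescue the criterion: the article states the rule, the rule governs the primary analysis, and FMI cannot do what is asked of it. That the sign of the error turns on an unstated reading itself shows that the rule is not properly fixed.

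**Conclusion.** The point holds as a minor defect in prespecification. From 100 to 500 imputations the systematic fall in FMI is about one eighth to one twelfth of its Monte Carlo SD at 100, so improvement in FMI cannot identify a better number.

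The consequence for inference is small. At an FMI near the reported missingness, the standard error is off by about 1% at most in either direction, and type I error lies between 0.049 and 0.053. At the planning extreme the standard error could be up to 3.6% too small or 1.5% too large, with type I error between 0.047 and 0.059.

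These figures assume that the grid means imputations, that missingness stands in for FMI, and, for type I error and the outer ends of the SE ranges, that the six sets are independent. They do not support calling the trial's inference invalid or the rule biased in one known direction. The mixing of iterations and imputations is a separate wording fault that the text should resolve.

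**What to change.** Replace the FMI selection rule with one number of imputations set in advance; 500 is already on the grid and leaves the least Monte Carlo error. State the number of MCMC iterations separately, so that chain length and number of completed data sets are no longer confused. Analyse only that set, and report FMI and Monte Carlo error as diagnostics that play no part in choosing the data.

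Possible wording: missing values will be imputed 500 times; the MCMC iterations are specified separately; all imputation-based analyses use this one set; FMI and Monte Carlo error are reported descriptively.

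The change costs nothing in patients, data collection or power. If the six sets would have been generated separately, it also saves computing: 500 imputations instead of 100 + 150 + 200 + 300 + 400 + 500 = 1,650. It should be made before the outcome data are analysed by group.

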In addition to the primary analysis, further sensitivity analyses will be performed. Analyses of intervention effects on all outcomes will be repeated using analysis of covariance, adjusted for baseline scores. In addition, per-protocol analyses excluding participants who violated the protocol will be conducted. The following protocol violations have been prespecified: (1) failure to download the app and complete the onboarding process in the intervention group, (2) reporting of using a similar digital health intervention during the intervention and follow-up period in the control group, (3) reporting of regular psychotherapy during the 8-week intervention period, and (4) noncompletion of postintervention or follow-up assessment. Subgroup analyses will be done to address potential heterogeneity.

To allow for adjustment of the sample size in this study (for lower dropout), an interim analysis can be performed. This can be done once the primary end point of 182 participants is available. With this sample size, the expected effect can be revealed with a probability of 85% at a significance level of α=10%. The interim analysis will be performed blinded, meaning that the variable “group membership” will be replaced by a dummy variable and the blinded data set will be analyzed by a person who is not part of the core study team and is unaware of the group assignment.

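### The primary analysis of 8-week PHQ-9 is an unadjusted t test; making the planned baseline-adjusted ANCOVA primary, with the stratification factors added, would gain precision at almost no cost

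*Protocol article*

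**What the plan says.** The Sample Size section defines the endpoint: "The primary end point is the between-group difference in depressive symptoms (PHQ-9 total score) after 8 weeks". It then names the test: "The effect regarding the primary end point will be determined by a 2-tailed" t test. The Statistical Analysis section repeats the choice for every endpoint, on multiply imputed data pooled by Rubin's rules: "The comparison of intervention effects on all outcomes will be done using" t tests.

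Baseline adjustment comes in the next paragraph, which opens "In addition to the primary analysis, further sensitivity analyses will be performed" and continues "Analyses of intervention effects on all outcomes will be repeated using analysis of covariance, adjusted for baseline scores". ANCOVA is therefore planned, but ranked below the t test, and its only named covariate is the baseline score.

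Under Procedures, randomisation is 1:1 and "stratified by sex (male, female, and diverse), diagnosis (F32.0, F32.1, F33.0, and F33.1), and previous psychiatric or psychotherapeutic treatment (yes and no"). Neither the t test nor the ANCOVA is said to include these factors. Textbox 1 lists the PHQ-9 sum score at randomisation among the recorded moderators, so the key covariate is available.

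Two other statements in the Statistical Analysis section bear on the point. Significant baseline differences are to be found by χ² and t "tests on baseline variables and accounted for in all analyses". Missing outcomes are to be imputed from the information collected at baseline.

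**The concern.** Baseline PHQ-9 is measured on the same scale as the outcome and usually predicts it. Leaving it out of the comparison leaves explainable variance in the error term, so the interval for the treatment effect is wider than the data require. Stratified allocation raises a related issue. Stratifying on prognostic factors balances them and so reduces the true sampling variance of the difference between arms, but an analysis that omits them still estimates the larger, unstratified variance. Its standard error is then somewhat too large.

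The sentence on significant baseline differences does not settle this. A plain t test has no place for covariates, so the sentence conflicts with the test named in the same section. The covariates in the primary model would also be unknown until the baseline tests had been run.

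At stake are the width of the primary confidence interval, some power if dropout is high or the sample size is cut, and a primary model that is fully fixed in advance.

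**Working it through.** **1. Inputs from the Sample Size section.** d=0.4, two-sided α=0.05, power 85%, dropout up to 60%, N=570. The Results section reports about 20% missing primary outcomes so far.

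**2. Reproducing the plan's figure.** A two-sample t test (noncentral t) needs 113.2, rounded up to 114 per arm, or 228 in total. 228/(1−0.60) = 570. The stated N is exactly that of an unadjusted t test, so the trial was sized without covariates.

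**3. Gain from adjusting for baseline.** With correlation r between baseline and 8-week PHQ-9, the ANCOVA residual variance is (1−r²) times the raw variance. The effective standardised difference is 0.4/√(1−r²), and the interval width is multiplied by √(1−r²). The article gives no r, so a range is assumed.

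| r | Variance removed (r²) | Interval narrower by 1−√(1−r²) | Power, 228 evaluable | Power, 456 evaluable |
|---|---|---|---|---|
| t test | – | – | 0.852 | 0.989 |
| 0.3 | 9% | 4.6% | 0.883 | 0.994 |
| 0.4 | 16% | 8.3% | 0.907 | 0.996 |
| 0.5 | 25% | 13.4% | 0.935 | 0.998 |
| 0.6 | 36% | 20.0% | 0.964 | 0.9996 |

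The 228 column corresponds to 60% dropout. The 456 column is 570 × (1−0.20). Both treat evaluable participants as a complete-case comparison and count baseline PHQ-9 only, not the strata.

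Put as sample size, 228 × (1−r²) gives 207, 192, 171 and 146 evaluable participants for the same 85% power at r = 0.3, 0.4, 0.5 and 0.6.

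**4. Effect of omitting the strata.** There are 3 × 4 × 2 = 24 strata. If they explain a share R² of outcome variance and allocation balances them, the t test in effect uses a critical value of 1.96/√(1−R²). The documents give no R². For an assumed 5% this is 2.011, an actual two-sided α of about 0.044. For an assumed 10% it is 2.066, an α of about 0.039. Balance within 24 strata, some of them sparse, will be imperfect, so these figures are towards the conservative end for each R².

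**5. What the baseline-testing rule recovers.** A simulation (10,000 runs per setting, 228 participants, d=0.4, baseline PHQ-9 as the only covariate, no missing data) compared always adjusting with adjusting only when the baseline test is significant at 5%.

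| r | Always ANCOVA | Adjust only if significant |
|---|---|---|
| 0.3 | 0.883 | 0.856 |
| 0.5 | 0.936 | 0.863 |
| 0.7 | 0.986 | 0.870 |

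The t test alone gives about 0.85, so the rule recovers little. With no true effect it rejects in about 4.4%, 4.2% and 3.5% of runs. It is conservative, not inflated.

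**The case against.** The strongest defence is that nothing here is invalid. The t test is prespecified, unbiased under randomisation and consistent with its own sample size calculation, and baseline-adjusted ANCOVA is already planned for every outcome. That stands. The point concerns which analysis should carry the conclusion.

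A reader might infer that the primary analysis makes no use of baseline data at all. The article does not support that. Baseline information feeds the imputation, and the promise to account for significant baseline differences extends to all analyses. But imputation affects only participants with missing outcomes, and the promise cannot be kept with a plain t test.

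A reader might also infer that the trial is underpowered. At full recruitment with the reported 20% missing, t-test power is already 0.989 and adjustment adds about one percentage point or less. The larger gains require either the planned 60% dropout or a smaller sample. The second is possible, since the Abstract gives 570 as an upper limit and the optional interim analysis exists to adjust the sample size for lower dropout, but it is not required.

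Finally, r is assumed. Enrolling only mild and moderate depression may narrow the spread of baseline scores and favour the lower end of the range. That also stands. If r is low, adjustment gains little, but it costs only a few degrees of freedom.

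**Conclusion.** The concern holds as one of efficiency and prespecification, not validity. The primary t test leaves out the baseline score and the stratification factors, and the rule for significant baseline differences does not make good the omission.

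For an assumed r of 0.3 to 0.6, the primary interval is wider than it need be: adjustment would narrow it by about 5% to 20%, whatever the sample size. The power gain at d=0.4 is roughly 3 to 11 percentage points at 228 evaluable participants and about 1 point or less at 456. To the extent that the strata predict outcome, the t test is mildly conservative, with an actual α of about 0.044 or 0.039 if they explain an assumed 5% or 10% of variance. It would be wrong to conclude that the treatment estimate is biased, that type I error is inflated, or that 570 is miscalculated. The change is worth making because it costs almost nothing.

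**What to change.** - Make the primary analysis a linear model (ANCOVA) of 8-week PHQ-9 on arm, baseline PHQ-9, sex, diagnosis and previous treatment, fitted in each imputed data set and pooled by Rubin's rules.
- State a fixed rule for pooling the sparse diverse level of sex, so that the model can be fitted whatever the counts.
- Delete the rule that tests baseline differences for significance and adjusts for those found. The prespecified covariates replace it.
- Keep the t test as a sensitivity analysis.
- Treat the secondary outcomes the same way, each with its own baseline value.

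The cost is a swap of rank between two planned analyses, three added covariates and one deleted sentence. No extra data are needed and the sample size can stay as it is. Because recruitment is under way, the change should be recorded as a dated amendment before outcomes are compared by arm, including at the optional interim analysis.
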